## 1.12 FLOWSHEET FOR MAIN PHASE OF STUDY: CONTINUOUS ART ARM (and those in SCT arm who resume continuous ART)

| WEEK                                              | Screening
-4 to -2 | Randomisation
0 | 4 | 12  | 24  | 36  | 48 | Further follow-up                       | End of study visit                         |
|---------------------------------------------------|-----------------------|--------------------|---|-----|-----|-----|----|-----------------------------------------|--------------------------------------------|
| Continuous ART arm                         |                       |                    |   |     |     |     |    |                                         |                                            |
| Signed informed consent                           | X                     | (confirm)          |   |     |     |     |    |                                         |                                            |
| Clinical assessment a                  | X                     | X                  | X | X   | X   | X   | X  | Every 12 weeks                          | X                                          |
| Tanner scales                                     |                       | X                  |   |     | X   |     | X  | Every 24 weeks                          | X                                          |
| Lipodystrophy assessment                          |                       | X                  |   |     | X   |     | X  | Every 48 weeks                          | X                                          |
| Local HIV-1 RNA viral load                        | X                     |                    | X | X   | X   | X   | X  | Every 12 weeks                          | X                                          |
| T cell lymphocyte subsets
inc. RO/RA phenotype | X                     | X                  | X | X   | X   | X   | X  | Every 12 weeks                          | X                                          |
| Biochemistry b                         | X                     | X                  |   | (X) | (X) | (X) | X  | As per local practise                   | X                                          |
| Haematology c                          | X                     | X                  |   | X   | X   | X   | X  | Every 12 weeks                          | X                                          |
| Lipids/glucose d                       |                       | X                  |   |     | X   |     | X  | Every 48 weeks                          | X                                          |
| Pregnancy Test e                       | X                     |                    |   |     | X   |     | X  | Every 24 weeks                          | X                                          |
| Plasma storage f                       | X                     | X                  | X | X   | X   | X   | X  | Every 12 weeks                          | X                                          |
| Cell storage f                         | X                     | X                  | X | X   | X   |     | X  | Every 24 weeks                          | X                                          |
| Adherence questionnaire                           | X                     |                    | X | X   | X   | X   | X  | Every 12 weeks                          | X                                          |
| Acceptability Questionnaire                       |                       |                    |   |     |     |     |    | If in SCT arm & re-start continuous ART | If in SCT arm & re-starting continuous ART |
| PedsQL™ Questionnaire                             |                       | X                  |   |     | X   |     | X  | Every 24 weeks                          | X                                          |

Notes: shaded boxes indicate visits where overnight fasting is required for blood lipids/glucose.

(X) – Indicates optional investigations.

*If insufficient blood is drawn, priorities are: local HIV-1 RNA, T cell subsets, plasma store, lipids/glucose, biochemistry, haematology*

(a) Clinical assessment: including height & weight (adjust doses), presence of adverse events and change in HIV disease stage (including clinical lipodystrophy).

(b) Biochemistry: Creatinine, Bilirubin, ALT, AST, Alkaline Phosphatase and Albumin. Calcium and Phosphate at baseline and annually thereafter.

(c) Haematology: Hb, MCV, WBC, Lymphocytes, Neutrophils, Platelets

(d) Lipids/Glucose: Triglycerides, Cholesterol (Total, HDL, LDL, VLDL), Glucose. Overnight fasting required at randomisation and weeks 24 and 48, and then every 48 weeks.

(e) Pregnancy Test: either a blood or urine sample. This test will be performed for all females of childbearing potential at screening and weeks 24 and 48 (then every 24 weeks) and at other time-points if required. The initial pregnancy test must be done within 72 hours of enrolment and its results must be received before randomisation.

(f) 16ml total blood draw for plasma and cell storage: 6.0ml in EDTA if plasma store only [see Manual of Operations for instructions for plasma and cell handling and storage].

**1.13 FLOWSHEET FOR LONG TERM FOLLOW UP:**

| TIMEPOINT AFTER FINAL MAIN TRIAL VISIT                                                        | Every 12-16 weeks post main trial | Annual long term follow up visit (48 weeks after final main trial visit) | Final follow up visit (Apr 2016-Jul 2016) |
|------------------------------------------------------------------------------------------------------|------------------------------------------|---------------------------------------------------------------------------------|--------------------------------------------------|
| Both arms                                                                                     |                                          |                                                                                 |                                                  |
| Clinical assessment a                                                                     | X                                        | X                                                                               | X                                                |
| Local HIV-1 RNA viral load b                                                              | X                                        | X                                                                               | X                                                |
| CRF completion                                                                                       | X                                        | X                                                                               | X                                                |
| Adherence questionnaire                                                                              | X                                        | X                                                                               | X                                                |
| Plasma and cell c storage (6 ml full blood in EDTA plus extra 10ml if cells being stored) |                                          | X                                                                               | X                                                |

**Notes:**

- (a) Clinical assessment: including presence of adverse events and change in HIV disease stage. Include CD4 count and document locally
- (b) Management of HIV-1 RNA viral load should continue as specified in Appendix 15
- (c) Cells storage at applicable sites

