## **1.6 Duration**

Young people will be recruited over 27 months and followed until the last randomised participant has completed 48 weeks of follow-up, at which point the main trial will be considered complete. Participants being followed after week 48 should be seen every 12 weeks until the main trial is complete. Participants randomised to the SCT arm should continue to follow the SCT strategy until the main trial is complete unless the clinician or the family have concerns which the clinician should discuss with the appropriate Trials Unit.

Stable and virologically suppressed young people who were randomised to SCT can continue SCT after completion of the main trial if agreed by the clinician and family at least until the results of the main trial become available. Management of HIV-1 RNA viral load should continue as specified in appendix 15.

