**1.11 FLOWSHEET FOR MAIN PHASE OF STUDY: SCT arm (after pilot fully recruited)**

| WEEK                                              | Screening
-4 to -2 | Randomisation
0 | 4 | 12  | 24  | 36  | 48 | Further follow-up             | End of study visit |
|---------------------------------------------------|-----------------------|--------------------|---|-----|-----|-----|----|-------------------------------|--------------------|
| SCT arm                                    |                       |                    |   |     |     |     |    |                               |                    |
| Signed informed consent                           | X                     | (confirm)          |   |     |     |     |    |                               |                    |
| Clinical assessment a                  | X                     | X                  | X | X   | X   | X   | X  | Every 12 weeks                | X                  |
| Tanner scales                                     |                       | X                  |   |     | X   |     | X  | Every 24 weeks                | X                  |
| Lipodystrophy assessment                          |                       | X                  |   |     | X   |     | X  | Every 48 weeks                | X                  |
| Local HIV-1 RNA viral load                        | X                     |                    | X | X   | X   | X   | X  | Every 12 weeks                | X                  |
| T cell lymphocyte subsets
inc. RO/RA phenotype | X                     | X                  | X | X   | X   | X   | X  | Every 12 weeks                | X                  |
| Biochemistry b                         | X                     | X                  |   | (X) | (X) | (X) | X  | As per local practise         | X                  |
| Haematology c                          | X                     | X                  |   | X   | X   | X   | X  | Every 12 weeks                | X                  |
| Lipids/glucose d                       |                       | X                  |   |     | X   |     | X  | Every 48 weeks                | X                  |
| Pregnancy Test e                       | X                     |                    |   |     | X   |     | X  | Every 24 weeks                | X                  |

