### **Secondary Outcomes:**

The efficacy and safety of SCT and continuous ART will also be compared through the analysis of HIV-1 viral load and T cell subsets measured locally at each protocol visit, the presence of mutations conferring resistance to drugs taken at randomisation or during the trial, changes in the stage of a young person's HIV disease (CDC classification – see Appendix 8) measured at trial entry and each protocol visit, and the presence of adverse events. To assess the advantages and disadvantages of the strategy, acceptability, quality of life and adherence to the randomised strategy will also be compared. Specifically, the secondary outcomes of the trial are:

- HIV-1 RNA  $< 50$  c/ml at 24 and 48 weeks.
- Number of HIV mutations present at week 4, 12, 24, 36 or 48 conferring resistance to drugs taken at randomisation or during the trial
- Change in CD4 (absolute and percentage) from randomisation to 24 and 48 weeks
- Change in ART (defined as any change from the ART regimen at randomisation)
- Grade 3 or 4 clinical and laboratory adverse events.
- ART treatment modifying adverse events (all grades).
- New CDC stage B or C diagnosis or death
- Changes in fasting glucose, cholesterol, triglycerides, LDL, HDL and VLDL levels through 48 weeks
- Adherence, acceptability, and quality of life over 48 weeks as assessed by patient completed questionnaires
- HIV-1 RNA  $\geq 50$  c/ml (confirmed on a separate sample within 1 week) at any time throughout follow up
- HIV-1 RNA  $< 50$  c/ml at 96 and 144 weeks.
- Adherence over the duration of the trial, as assessed by patient completed questionnaires.
- Change in CD4 (absolute and percentage) from randomisation to 96 and 144 weeks.
- 

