## **4.3 Data collection and handling**

Data will be recorded on CRFs; the top copy/original (or a scan of the original) should be sent to the appropriate Trials Unit for data entry and a copy kept at the local clinical centre. The type of data to be recorded is detailed in the Assessments and Follow up section (section 8). Data from the CRFs will be entered onto databases held at the co-ordinating Trials Units, and exported into Stata for analysis. After completion, adherence and acceptability questionnaires should be sent to the appropriate Trials Unit for data entry.

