## **8.10 Long term follow up**

The long-term impact of SCT in HIV-1 infected young people is unknown. Following the young people enrolled in BREATHER for two years after the main trial is completed will provide valuable data on the long-term effects of taking weekends off treatment compared to continuous treatment, and whether there is any long-term impact on subsequent disease progression and efficacy of future treatment.

Routine clinical data will be collected and 12-16 weekly HIV-1 RNA viral load monitoring will be funded for participants in both arms where this is not local standard of care. Adherence questionnaires will be completed every 12-16 weeks (see flowsheet 1.13). A plasma sample and cells (where applicable) will be stored at the annual (48 weeks after the final main study visit) and final long term follow up visit. Management of HIV-1 RNA viral load should continue as specified in appendix 15.

Investigators will continue to be responsible for safety reporting as in the main trial (see section 10).

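### The long-term follow-up schedule does not secure the CD4 count and percentage that the week 96 and week 144 secondary outcome needs

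*Combined protocol and SAP*

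**What the plan says.** **Outcome.** Sections 1.4, 4.2 and 11.2 each list as a secondary outcome "Change in CD4 (absolute and percentage) from randomisation to 96 and 144 weeks".

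**Main trial.** Flowsheets 1.11 and 1.12 carry a row for "T cell lymphocyte subsets", measured at each scheduled visit, every 12 weeks after week 48 and at the end-of-study visit. The pilot flowsheets do the same. Section 8.4 defines the test as including CD4, both absolute and percentage. Section 1.6 sets the length of this phase: "Young people will be recruited over 27 months and followed until the last randomised participant has completed 48 weeks of follow-up", and "Participants being followed after week 48 should be seen every 12 weeks until the main trial is complete".

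**Long-term follow-up.** Flowsheet 1.13 has rows for clinical assessment, viral load, the CRF, the adherence questionnaire and stored samples, but none for T cell subsets. CD4 appears only in note (a), under clinical assessment: "Include CD4 count and document locally". Section 8.10 says "Routine clinical data will be collected and 12-16 weekly HIV-1 RNA viral load monitoring will be funded for participants in both arms" and does not mention CD4. The same flowsheet requires "CRF completion" at every long-term visit, and section 4.3 says "Data will be recorded on CRFs; the top copy/original (or a scan of the original) should be sent to the appropriate Trials Unit".

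**The concern.** The outcome needs two quantities, count and percentage, at two times, held centrally so that the Trials Units can analyse them. The long-term schedule asks for one of the two and tells the site to document it locally. The opening of section 8 sends readers to the flowsheets, 1.13 included, for what each visit requires, so a site following the protocol would look there and find nothing more.

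At stake is how much of the cohort informs the long-term immunological comparison. Section 8.10 calls the long-term impact of SCT unknown and gives that as the reason for the extra two years. If usable CD4 data came only from the main trial, the week 96 and week 144 results would describe the participants who entered earliest.

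**Working it through.** The documents state no figure for the number of participants with CD4 data at weeks 96 or 144, so there is none to reproduce. The check is how many participants depend on the long-term schedule at each time.

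**Inputs**
- Accrual R = 27 months (section 1.6) = 27 × 365.25 / (12 × 7) = 117.4 weeks.
- The main trial ends 48 weeks after the last randomisation (section 1.6), so T = 117.4 + 48 = 165.4 weeks after the first.
- Planned size: 160 to 220 participants (section 11.3).
- Accrual pattern: not given. Uniform accrual is assumed as the base case, with other patterns as a range.

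**Formula.** A participant reaches week w inside the main trial if randomised in the first T − w weeks. Under uniform accrual the share is f = (T − w) / R, and the share that depends on flowsheet 1.13 is 1 − f.
- Week 96: f = (165.4 − 96) / 117.4 = 69.4 / 117.4 = 59%, leaving 41%.
- Week 144: f = (165.4 − 144) / 117.4 = 21.4 / 117.4 = 18%, leaving 82%.

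With 160 participants these shares are about 65 and 131 people; with 220, about 90 and 180.

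**Other accrual patterns.** Linear ramp-up gives f² inside the main trial; linear ramp-down gives 1 − (1 − f)². The pilot pattern assumes 30 participants in 8 months, a one-month hold, then uniform entry over 18 months. The 30 and the hold are in the protocol (sections 4.1 and 11.5); the durations are assumptions.

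| Assumed accrual | Week 96 after main trial | Week 144 after main trial |
|---|---|---|
| Uniform | 41% | 82% |
| Pilot, hold, then uniform to 160 | 50% | 88% |
| Pilot, hold, then uniform to 220 | 53% | 92% |
| Linear ramp-up | 65% | 97% |
| Linear ramp-down | 17% | 67% |

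**Visit window.** Allowing an assumed 6 weeks either side, uniform accrual gives 1 − 75.4 / 117.4 = 36% at week 96 and 1 − 27.4 / 117.4 = 77% at week 144.

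**Reach of long-term follow-up.** Two further years take even the last entrant to about 48 + 104 = 152 weeks, so both time points lie within planned follow-up for those who consent. The gap is in what is recorded, not in how long people are followed.

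**Who the early entrants are.** The amendment history in section 18 puts the end of recruitment at the end of June 2013, so the main trial ends about 1 June 2014. Counting back, week 144 falls inside it only for entries before about late August 2011, and week 96 only for entries before about late July 2012. Version 1.5 (December 2011) first admitted previous dual therapy, and version 1.6 (29 June 2012) raised the upper age limit to 24. Main-trial CD4 at week 144 would therefore include nobody enrolled under either change, and at week 96 almost nobody from the added ages.

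**The case against.** The strongest reply is that the data may well reach the Trials Units. Note (a) places CD4 within the clinical assessment, a CRF is due at every long-term visit, and CRFs are sent centrally. The CRF fields are not in the documents. The amendment history names Tanner scales, routine blood counts and biochemistry as not needed in long-term follow-up, and CD4 is not on that list. Section 8.4 lists CD4 percentage among the trial's tests and, unlike the lipid row beside it, does not limit it to the main trial. Sites must give access to source data, so locally held values can be retrieved.

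Much of this stands, and it rules out three stronger readings that a reader might infer:
- *That most participants will have no central CD4 data.* Central capture is unspecified, not shown to be absent. The percentages above are shares that depend on the long-term schedule, not shares with missing data. A majority depends on it at week 144 under every pattern tried; at week 96 that turns on the accrual pattern, and under uniform accrual it is a minority.
- *That CD4 percentage will not exist in long-term follow-up.* The schedule does not request it, but section 8.4 leaves room for it to be measured.
- *That the comparison between arms would be biased.* Entry date determines who falls inside the main trial, and both arms recruit concurrently 1:1 in permuted blocks. The early subset therefore remains a randomised comparison.

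The reply does not remove the mismatch. Section 8.4 sets no visits, and the only CD4 instruction specific to long-term follow-up says to document the count locally. The separate SAP that section 11.6 promises cannot analyse values that were never sent.

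**Conclusion.** The point holds as a mismatch between a stated secondary outcome and the schedule meant to supply it. For participants whose week 96 or week 144 falls after the main trial, the plan does not secure central CD4 count and does not request CD4 percentage. Under uniform accrual these are about 4 in 10 participants at week 96 and 8 in 10 at week 144. The ranges of 17-65% and 67-97% reflect the unknown accrual pattern; visit windows would lower the shares somewhat.

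The consequence is possible loss of precision and a population narrowed to early entrants. The primary outcome, the week 24 and 48 CD4 outcomes and the week 96 and 144 viral load outcome are not affected. If the long-term CRF already has both CD4 fields, the problem reduces to the wording of note (a) and section 8.10.

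**What to change.** Change note (a) of flowsheet 1.13, and section 8.10 with it, so that CD4 absolute count and percentage are recorded on the CRF at least at the visits nearest weeks 96 and 144, counted from randomisation. A CD4 entry at every 12-16 weekly visit is more than the outcome requires. Ask sites for values they already hold in those two windows. Where percentage was not measured, report the absolute count only and state the number contributing in each arm at each time.

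The cost is two CRF fields and a data request. Note (a) already asks for a CD4 count at these visits, so no extra visit is needed.

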## 2 BACKGROUND

### 2.1 Introduction

Antiretroviral therapy (ART) has dramatically improved the prognosis for HIV-infected children. It has reduced early morbidity and increased survival, with more than 80% of children expected to reach adulthood [1]. HIV has been transformed from a devastating, rapidly progressive lethal condition into a chronic disease. Now the challenges for the treatment of HIV-infected children are to (i) maximise benefit of ART which prevents illness and encourages growth and development, (ii) minimise long-term drug toxicity and (iii) minimise the development of drug resistance so that children continue to have therapy options as they move through adolescence and into adulthood and (iv) to improve quality of life as much as possible for young people on ART.

Paediatric ART guidelines in 2008 advocate starting ART in infancy (<12 months of age) in all those diagnosed because of high risk of disease progression, following recent results from a randomised control trial [2-5]. Even if ART is not started early, vertically infected children face many more years of ART, often given throughout childhood, compared to adults. Therefore, there is a growing population of older children and young people who have already been on ART for many years and are continuing to face the challenge of taking daily medication [6].

A major challenge for young people with HIV, as for any chronic illness, is maintaining long-term adherence to treatment regimens [7-9]. The importance of adherence to the long term success of ART in maintaining virological suppression and prevention of emergence of resistance has been established [10-17]. However, experience with HIV-infected young people suggests that with current treatment strategies, adherence rates fall far below the 90-95% adherence associated with long term success [18-20]. Furthermore some studies have demonstrated a decline in adolescent adherence over time associated with duration on therapy [18]. Impediments to adherence for young people have been broadly categorised into two main groups; problems with medication such as taste and palatability issues, and adherence difficulties related to social situations [21]. While there have been considerable attempts to improve drug formulations, thus partly addressing the first impediment, the social dimensions are more complex; interference with daily life recurs as a common theme in assessments of poor adherence in young people.

New treatment strategies which promote adherence, minimise development of resistance, reduce long-term drug exposure while improving quality of life are required for young people 'burning out' on daily ART regimens. Approaches to achieve this include: (i) simplification of therapy (i.e. minimising the number of pills or swapping from twice to once-daily dosing), (ii) treatment interruptions (for example, based on levels of CD4 as in the PENTA 11 trial [22]; not currently advocated) and (iii) very short treatment interruptions (particularly at inconvenient times for taking medication such as weekends) with the aim to maintain viral suppression; one such possible strategy is to give therapy during the week but allow a break at the weekend.

